#### Subproject 2 (qualitative study with mental health service users)

Following an explanatory sequential design, the selection of respondents in subproject 2 is guided by the results of the quantitative survey conducted in subproject 1. We will select participants from the subproject 1 sample based on the extent and forms of violence experiences as indicated in the standardized questionnaire, as well as sociodemographic characteristics. The sample size is determined by theoretical saturation of the phenomenon being studied. Based on previous experiences, we anticipate a sample size of 30–40 interviews (n=15–20 women; n=15–20 men).

#### Subproject 3 (qualitative study and quantitative survey with mental health professionals)

To capture both the subjective and collective perspectives of mental health professionals, subproject 3 employs an exploratory sequential design, beginning with qualitative interviews followed by standardized measures. Recruitment takes place at the participating clinics, where staff members from relevant professional groups involved in direct patient care will be invited to take part. For the qualitative study part, we will recruit participants who exhibit a broad range of sociodemographic and professional characteristics (gender, age, professional experience, treatment setting). We anticipate conducting approximately 30 to 40 interviews and about 3 to 4 focus groups. The final sample size will be determined by theoretical saturation. For the following quantitative part, a standardized questionnaire will be administered to assess frequencies and correlations of mental health professionals’ attitudes. Staff members will be invited to participate in an online survey.

### Data collection and study instruments

#### Subproject 1 (quantitative cross-sectional survey with mental health service users)

Study participants complete the questionnaires on a tablet or using paper-pencil in the clinic. Study staff are available for inquiries. Following a participatory approach, the questionnaire was tested and reviewed in collaboration with peer researchers. Data are collected and managed using REDCap electronic data capture tools hosted at Leipzig University. REDCap (Research Electronic Data Capture) is a secure, web-based software platform designed to support data capture for research studies, providing 1) an intuitive interface for validated data capture; 2) audit trails for tracking data manipulation and export procedures; 3) automated export procedures for seamless data downloads to common statistical packages; and 4) procedures for data integration and interoperability with external sources (39). We will use the following instruments:

The Patient Health Questionnaire (PHQ-D) (40) to assess impairments due to physical and psychological symptoms.Psychiatric and psychotherapeutic hospitalization and treatment experiences as well as diagnoses and symptoms are queried.Substance use is assessed using short forms of AUDIT (41) and DUDIT (42).The German version of the Self-Stigma of Mental Illness Scale (SSMI-SF) (43, 44).One item to assess the general satisfaction with life (45).ISEL-12 (46) to measure social support, and additional items designed with participatory researchers to assess other resources.Questions on sociodemographic characteristics: age, nationality, socioeconomic status (47, 48), sex and gender (similar to 49), family status, sexual orientation (similar to 50, 51), and experienced discrimination.Social desirability is assessed using the Social Desirability Gamma Scale (52).Experiences of violence: a survey on the type, frequency, and context of violence (violence as well as victimization experiences during the last year and over the lifetime), compiled in accordance with (53–55).

Violence was operationalized as experiences of physical violence, sexual violence, and threats of violence in line with definitions from the WHO World Report on Violence and Health (56), and assessed using standardized self-report items adapted from the MacArthur Community Violence Screening Instrument (MCVSI) (53–55, 57). The questionnaire includes items assessing experiences of physical violence (e.g., being hit, kicked, robbed, or threatened with a weapon) and sexual violence (e.g., sexual coercion), based on and adapted from items provided by Harris et al. (54) and components of the MCVSI. Respondents are asked about both lifetime and past-year experiences, as well as the context and relationship to the perpetrator.

#### Subproject 2 (qualitative study with mental health service users)

Selected participants of subproject 1 who consented to be interviewed in the qualitative study part will be contacted and invited to participate. Narrative-biographical interviews will be conducted either face-to-face or via video call, using an encrypted provider that complies with the requirements of the German General Data Protection Regulation (DSGVO). The interviews will be conducted by researchers trained and experienced in qualitative interviewing.

Narrative-biographical interviews enable a valid exploration of individual structures of meaning and significance. The open narrative prompt, focusing on experiences of violence, elicits an autobiographical narration that aligns with the storyteller’s relevance systems not constrained by the researchers’ preconceptions. An interview guide is developed, based on relevant literature and validated through participative qualitative research workshops, which include researchers from diverse mental health fields as well as mental health service users. The use of this guide ensures that relevant aspects are addressed based on the current state of research and (preliminary) findings from subproject 1, e.g. dealing with client’s disclosure of violence experiences. The interviews will be audio-recorded and fully transcribed. Additionally, spontaneous field notes will be taken immediately after the interview as part of the research diary.

#### Subproject 3 (qualitative study and quantitative survey with mental health professionals)

We collect data on the subjective and collective perspectives of mental health professionals on their client’s violence experiences using qualitative interviews, focus groups, and standardized questionnaires.

Qualitative approach: The guidelines for the interviews and focus groups consist of predominantly open-ended questions about everyday experiences, as well as semi-structured questions to enhance comparability. Data analysis is conducted using content-analytical approaches and supplemented with reconstructive analytical tools. The results are validated through intersubjective exchange and consensus alignment of interpretations during regular participatory research workshops.

Quantitative approach: Based on both the findings from the quantitative survey in subproject 1 and initial qualitative findings in subproject 2 and 3, a questionnaire will be developed to assess and quantify professionals’ perspectives on facilitators and barriers related to dealing with their clients’ experiences of violence. Stigmatizing attitudes will be captured by the German Version of the Community-Attitudes-Toward-the-Mentally-Ill inventory (CAMI) (58).

### Promotion of study participation

Potential study participants will be informed about the study in a separate meeting prior to participation, where they will be encouraged to take part. Study staff will introduce the study and explain the procedures face-to-face in either group or individual settings on each ward. Study information and consent forms will be obtained from participants. In addition to the written consent forms, information will be provided in a concise format through a study flyer. Study participants will complete the questionnaires independently, either on a tablet or on paper, while study staff remain nearby to provide support in case of questions or emotional stress reactions. In subproject 1, after completing the survey, participants can choose whether they would like to be re-contacted to participate in subproject 2. If they agree, they will receive an email a few weeks later inviting them to take part in the qualitative study (subproject 2). In the qualitative study parts (subproject 2, subproject 3), participants receive an incentive of 30€ for participation. Participants from the general population will be contacted by USUMA and conclude the survey online.

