Mental health professionals are in a central position to identify victimization among service users and to provide adequate support. However, despite the strong evidence for the increased risk among people with SMI and the detrimental effects of victimization for individuals and their families (20), victimization among people with SMI is often neither systematically recorded nor considered in mental health care (21–23). Victims of violence identify key barriers to disclosure, including feelings of shame and guilt, delayed realization of the violence, fear of subsequent violence, and inappropriate reactions to the disclosure (24). Mental health professionals report feeling overwhelmed and uncertain in recognizing and dealing with experiences of violence, fearing negative consequences for the victims, or refer to practical barriers such as a lack of time (24). In an Australian study, professionals were found to have varying responses to disclosures of sexual assaults, including disparaging views that led to minimizing, ignoring, or blaming the disclosures, and while some acknowledged the prevalence of sexual violence, they felt ill-equipped to respond appropriately (25). The lack of mental health professionals’ engagement with the phenomenon of service users’ victimization brings about three significant problems: First, it impedes the early detection and addressing of experiences of violence in medical history taking and therapy, which is crucial for trauma-therapeutic interventions and support, e.g. connecting to specialized services (26). Second, there is a risk for re-traumatization that can occur in inpatient settings, particularly in regard with coercive measures. Seclusion and/or restraint can have deleterious physical and psychological consequences including post-traumatic stress disorders particularly for people with previous experiences of victimization (26). However, studies on re-traumatizing experiences during inpatient treatment are scarce, and the role of gender remains widely unclear. Third, the lack of awareness and engagement of mental health service providers hinders the development of structural measures to prevent and reduce the risk of people with SMI becoming victims of violence within and without mental health settings. As the outlined background on victimization of people with SMI demonstrates, developing effective measures to prevent victimization requires a comprehensive understanding of the complex and multifaceted underlying mechanisms of violence, as well as an understanding of the factors influencing the disclosure of such experiences in mental health settings.

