### Epistemological and methodological framework of the study

This mixed-method study is positioned at the intersection of sociological violence research, social psychiatry, and gender studies. Social psychiatry emphasizes the social, biographical, and cultural influences on the development, course, and management of mental illness, and highlights the reciprocal relationships between subjects and their environments (30). In turn, sociological violence research conceptualizes violence as an intentional act of power embedded in social orders and shaped by situational and contextual conditions (31). Following Popitz’s definition of violence as an intentional act leading to physical harm (32), the study focuses on physical violence (e.g., hitting, kicking, robbery, armed assault) and sexual violence (e.g., harassment, attempted rape), including domestic and partner violence. Methodologically, the study combines context-centered approaches, which examine macro-social and cultural conditions (e.g., poverty, norms, inequality), with situation-centered approaches, which reconstruct interactions and subjective interpretations of violence on the micro-sociological level. Particular emphasis is placed on the biographical embedding of violent experiences, recognizing their temporal structuring and dynamic unfolding across the life course. By linking social, institutional, and biographical factors, this design allows us to explore how prior experiences, life trajectories, and environmental contexts intersect to shape patterns of victimization among people with severe mental illness. From a gender perspective, the framework draws on feminist and sociological theories that interpret male violence against women as an expression of dominance, while situating violence among men within the construction and negotiation of hegemonic masculinities (33). This dual lens enables the analysis of both hetero- and homosocial dimensions of violence. At the same time, the framework transcends dichotomous attributions of (male) perpetrators and (female) victims by addressing victim-offender overlaps and the situational as well as biographical dynamics that link victimization and violent behavior. In this way, mechanisms of inversion between victim and perpetrator roles can be identified, and the impact of socialization processes or continuous exposure to violence on trajectories of vulnerability and violent behavior can be systematically addressed.

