### Participants and eligibility criteria

The standardized survey of subproject 1 includes people with SMI of legal age (18+ in Germany) who are undergoing treatment in one of the participating clinics at the time of recruitment. The term “people with SMI” refers to individuals diagnosed with mental illness that significantly impair their ability to function in daily life. These conditions often include disorders such as schizophrenia, bipolar disorder, or severe major depression, and typically require (long-term) treatment and support (35). For our study, we operationalize the term “people with SMI” based on the indication for psychiatric hospitalization, as well as outpatient treatment in a psychiatric hospital or outpatient service, which is considered an indicator of “severe mental illness”. Synonymously we use the term “mental health service user”. Exclusion criteria include language barriers and cognitive deficits, such as dementia or intellectual disabilities.

The qualitative study of subproject 2 includes persons of legal age who took part in the standardized survey in subproject 1. The selection of participants is based on the extent of violence experienced as indicated in the standardized questionnaire. Participants who report experiences of physical or sexual violence will be considered eligible for the qualitative interviews. The phrase “beyond a cut-off” refers to the self-reported occurrence of at least one experience of physical or sexual violence in the questionnaire. Final selection will additionally consider the forms of violence reported and sociodemographic characteristics in order to ensure heterogeneity of cases.

Individuals who meet these criteria and agree to participate in a narrative-biographical interview will be included. In subproject 3, mental health professionals from the fields of nursing, psychology, social work, and medicine who are employed at one of the participating clinics will be recruited for the qualitative interviews and focus groups, and for the subsequent quantitative survey.

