### Ethics

#### Informed consents

Each potential study participant will be informed verbally and in writing about the study’s aims, procedures, data policies, and potential risks. A copy of the information sheet will be provided to the study participants. After ensuring that they fully understand the study details and all their questions have been answered, informed consent will be obtained separately for each subproject. In subproject 1, participants from the general population will provide informed consent by checking a box at the beginning of the online questionnaire, while patients in psychiatric hospitals will sign an informed consent form. In subproject 2 and subproject 3, participants will send their signed consent form by email or post. Respondents will be assured that they can refuse to participate or withdraw consent at any time without facing any adverse consequences.

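### Interview re-contact by email only, with signed consent returned by email or post, could expose a disclosure of violence and leaves participants who find that route unsafe no option but to decline

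*Protocol article*

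**What the plan says.** All of this is in the protocol article.

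- **Scope.** The section on the epistemological and methodological framework defines the violence under study as physical and sexual, "including domestic and partner violence".
- **Who is interviewed.** Under Participants and eligibility criteria: "Participants who report experiences of physical or sexual violence will be considered eligible for the qualitative interviews". The cut-off is "the self-reported occurrence of at least one experience of physical or sexual violence in the questionnaire".
- **Opt-in.** Under Promotion of study participation, after the survey "participants can choose whether they would like to be re-contacted to participate in subproject 2".
- **Channel and timing.** The same section says that, if they agree, "they will receive an email a few weeks later inviting them to take part in the qualitative study (subproject 2". No other channel is named.
- **Who is contacted.** The subproject 2 part of Data collection and study instruments words it differently: "Selected participants of subproject 1 who consented to be interviewed in the qualitative study part will be contacted and invited to participate".
- **Consent.** Under Informed consents, for subprojects 2 and 3, "participants will send their signed consent form by email or post".
- **The barrier the authors cite.** The Introduction lists "fear of subsequent violence" among the reasons victims do not disclose.
- **Harms.** The Harms section expects no adverse events. The measures it describes are for emotional reactions and suicidality.

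**The concern.** The people approached for subproject 2 include some who may still live with the person who hurt them. The plan reaches them through a channel that a household member may be able to read, some weeks after a survey completed in a clinic. Some will by then be back at home; how many is an assumption, because the article gives no lengths of stay. A named, signed form for a study about violence then travels by email or post.

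Two things are at stake. The first is safety and confidentiality: a disclosure made in a protected setting could become known to the person it concerns. The second is the range of cases. If those with most reason to fear exposure decline re-contact, accounts of ongoing partner violence and of disclosure under threat could be thin in a subproject that asks about gender, re-victimization and disclosure.

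**Working it through.** No formula applies. The point depends on no error rate, effect size or sample size, so the check is to set the sections side by side.

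1. **Does the stated route carry material that could identify the topic?** Informed consents requires each potential participant to be informed in writing about the aims, to receive a copy of the information sheet, and to consent separately for each subproject. The Outcomes section gives the aim of subproject 2 as the subjective meaning of violence experiences. Written material naming that topic will therefore exist for subproject 2, and a signed form is returned through the participant's own email or post. The article does not say how the blank form and information sheet reach the participant.

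2. **Is the route protected elsewhere in the text?** Data collection requires an encrypted, data-protection-compliant provider for video interviews. Nothing comparable is stated for the invitation or the return of consent. The Confidentiality section deals with forms and data once stored. The Harms section does not consider exposure to a household member.

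3. **Does the opt-in remove the risk?** It reduces it, because nobody is emailed without agreeing. But the choice described is yes or no to re-contact, with email as the only form it takes. A person with a monitored mailbox can protect themselves only by saying no.

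4. **Does receiving the email reveal a disclosure?** The text is not consistent on who gets it. Promotion of study participation, read literally, emails everyone who agrees, so receipt would say nothing about survey answers. Data collection limits contact to selected participants, and the subproject 2 part of Recruitment and sample size calculation bases selection on the violence reported. Under that version an invitation goes only to people who reported violence. Even then, a reader of the mailbox would need either telling content in the message or knowledge of the eligibility rule.

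5. **What could selection do to the results?** Recruitment and sample size calculation sets subproject 2 as a purposive sample to theoretical saturation, with 30–40 interviews expected (15–20 women and 15–20 men). It produces no prevalence estimate, so there is none to bias. Purposive choice can draw only on people who accepted the route, and saturation among them cannot show that a type of case is missing from the pool. The exposed output is the typology described under Qualitative data analysis.

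6. **How many people are concerned?** The documents fix one number: all 30–40 interviewees are to return consent by email or post. The number living with a violent person who can read their mail cannot be derived from anything in the article.

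**The case against.** The strongest reply has three parts.

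**Voluntary and operational.** Participants decide about re-contact after the survey, with study staff nearby, and only those who agree are contacted. The consent form is outgoing: the participant sends it, and can choose between email and post. Neutral subject lines and safe-contact items usually sit in the full protocol or ethics file, which are not shown. This largely stands as a limit on the point: nobody can conclude from the article that the study lacks such arrangements. It does not remove the point, because the article states the channel, the timing and the consent return, and those stated choices are what is questioned.

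**Stronger readings that the documents do not support.** A reader might infer that the invitation itself shows that the recipient reported violence. The wording, sender and subject line are not given, and one of the two descriptions has everyone who agrees receiving the email. A reader might also see a conflict with the locked storage and restricted access described under Confidentiality. That section concerns stored forms and data; a form in transit contradicts neither.

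**Selection is not shown.** A reader might state as fact that the route selects against current victims of partner violence. No figure supports that. The direction is plausible and no more, and the subproject studies whole biographies, not only ongoing violence. Nor would multiplying assumed prevalence and opt-in rates help: it would count everyone with any lifetime violence who agrees to re-contact, which is not the group at risk.

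**Conclusion.** The point holds as a possible safety and confidentiality risk in a stated procedure, with a possible narrowing of the case range in subproject 2. It is not a demonstrated breach, an internal contradiction on confidentiality, or a bias in any estimate; subproject 1 is untouched.

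It rests on two assumptions: that some eligible participants share a mailbox or household with a violent person, and that some of the material in transit would identify the topic. The first is in line with the study's own scope and the barrier it cites. The second follows in part from the requirement for written information on the aims. The size of either effect cannot be estimated from the article. Separately, the two descriptions of who is contacted differ and need reconciling. The change is worth making because the potential harm is serious and the cost small.

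**What to change.** - **Promotion of study participation:** add a safe-contact choice to the re-contact form (phone, email, post or an appointment in the clinic, and whether messages may be left). Use a neutral sender and subject line that do not mention violence. Offer willing participants the subproject 2 information sheet and consent form in the clinic, where staff already meet them face to face.
- **Informed consents:** besides email and post, allow consent to be signed in person or uploaded by encrypted link.
- **Promotion of study participation and the subproject 2 part of Data collection:** state in both whether all who agree, or only selected participants, are contacted.
- If such arrangements already exist in the full protocol or ethics file, one sentence in the article saying so would answer the point.

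The cost is slightly more handling time per person and a minor notification to the ethics committee. No outcome, sample size or analysis changes. By the article's dates the change falls during ongoing recruitment: 250 of 500 survey participants were included at submission, and subproject 2 recruitment began in August 2024 with interviews to August 2025. It would therefore protect only those not yet approached. For the others, the results paper should describe the route used and name the possible narrowing of cases as a limitation.
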